**Methods:**

A two-arm, parallel, open-label design, with the waiting-list control group receiving treatment as usual will be conducted. Participants (N = 70) meeting eligibility criteria will be randomly assigned to the FULLSENSE intervention or a waiting-list control group. Primary outcomes will assess the intervention’s acceptability, usability, and feasibility. Secondary outcomes will evaluate preliminary efficacy in improving sexual satisfaction, functioning, pleasure, and reducing sexual distress, while cognitive and neurophysiological assessments will allow us to explore functional connectivity and correlates of implicit cognition and interoception. Data collection will include self-reported measures and neurophysiology assessments for a nested sample.

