### Participants and eligibility criteria

To be eligible for randomization, participants must be adults (≥ 18 years old) of all genders and sexual orientations who have daily access to an internet-connected device, present a distressful sexual complaint over the last 6 months, do not present severe psychopathological (i.e., depression, anxiety), and neurological symptoms, thus not concurrently engaging in therapy (i.e., psychoactive medication) to alleviate sexuality-related issues, or cognitive-behavioral therapy for other psychological issues or in any other clinical study or trial. Participants who are underaged (< 18 years old), or with no internet access, without distressful sexual complaints, or with sexual complaints lasting less than 3 months, presenting severe psychopathological or neurological symptoms, with unstable medication usage over the last 3 months, engaging in sexuality-related other psychological intervention or clinical study or trial, will be excluded. A subsample of 20 participants from the intervention group will be invited to undergo an on-site laboratory data collection, based on the following inclusion criteria: age between (18-40 years), right-handed; reporting enjoyment of pornographic clips with actors of white ethnicity; not using medications or drugs that can interfere with brain activity, not do regular alcohol or drug use, including cannabis. The inclusion criteria for the laboratory sub-sample are based purely on technical and methodological standardization requirements for neurophysiological studies The specific visual stimuli used (featuring actors, typically white) are employed to ensure comparability with standardized, validated stimulus sets. These constraints are fully disclosed and approved by the Ethics Committee.

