The total sample size of (35 per arm) is **not intended for statistical power to detect treatment efficacy**. Consistent with recommendations for pilot trials, this sample size is adequate to assess the primary outcomes of **feasibility, acceptability, and usability**, and to provide a robust **estimation of effect sizes and attrition rates** necessary for calculating the required sample size of a future, fully powered definitive trial The study employs a within-subject design with a high number of trials per participant and fine-grained EEG/ERPs measures, which substantially increases statistical power. This approach allows for the detection of subtle intervention-related effects at the individual level and minimizes inter-individual variability. From a statistical standpoint, the large number of repeated measures per participant provides a rich dataset for reliable estimation of within-person changes, even with a smaller N.

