### Recruitment, enrollment, and randomization

Potential participants will be identified via patient partner organizations (e.g., the Portuguese Society of Clinical Sexology), university mailing lists, faculty newsletters, patient conferences, and social media platforms. Clinical centers will be notified about the study and supplied with promotional materials that guide interested people to the recruiting website/link for further information and registration. Participants will be invited to participate by filling in an expression of interest survey. A consent form will be executed during registration, followed by the eligibility criteria (T0) screening administered via a telephone interview (LimeSurvey GmbH, n.d.). After completing the online baseline assessment (T1), participants fulfilling all eligibility criteria will receive an informative audiovisual material through email. Such a video will contain a step-by-step guide on how participants will access, use, and complete the program. Maximal procedure randomization will be implemented by a team member using computerized software to create allocation tables (Clinical Trial Randomization Tool, n.d). Participants will be randomly allocated 1:1 to the two study arms (Figure 1). Randomization will also allocate a nested sample (n = 20) to an embedded assessment moment (T1 and T2). This sample will undergo complementary laboratory-based assessments intended to explore potential intervention-related changes in neural activity associated with cognitive and behavioral aspects of sexual response and sexuality in general. Measurements will encompass EEG functional connectivity and exploration of ERPs of sexual implicit cognitions (through an Implicit Association Task). Laboratory tasks will also include a physiological (thermography) plus self-reported body-heat sensations (genital temperature) assessments, intending to explore the relation between both variables as representative of sexual interception abilities.

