After completing the online baseline (T1) assessment, participants meeting eligibility criteria will be registered and randomized, following an appointment with the assigned research member (Psychologist) to provide program access, examine the program’s framework (Figure 2), present the baseline findings, and establish therapeutic goals. The primary outcomes of this pilot trial are acceptability, usability (System Usability Scale (SUS) (Bangor, Kortum, & Miller, 2008) and feasibility measures (i.e., recruitment, randomization, retention, and adherence rates). Acceptability will be assessed in postintervention semistructured interviews. Secondary outcomes will evaluate preliminary efficacy on sexual beliefs (Sexual Dysfunctional Beliefs Questionnaire (SDBQ); Nobre & Pinto‐Gouveia, 2003), sexual satisfaction (Global Measure of Sexual Satisfaction (GMSEX); Lawrance & Byers, 1995), function (Index of Erectile Function (IIEF); Rosen et al., 1997b); and Female Sexual Functioning Index (FSFI); Rosen et al., 1997a), pleasure (Sexual Pleasure Scale (SPS); Sanchez, Crocker, & Boike, 2005) and distress (Female Sexual Distress Scale-Revised (FSDS-R); Derogatis et al., 2002). Additionally, participants will complete a self-report questionnaire to provide their sociodemographic and sexuality-related behavioral data, including age, gender, relationship status, religion, education, sexual orientation, and frequency of sexual activities. Changes in potential transdiagnostic factors, namely interoceptive awareness (Multidimensional Assessment of Interoceptive Awareness (MAIA; Mehling et al., 2012), trauma screening questionnaire (Posttraumatic Stress Disorder Checklist for DSM-5 (PCL-5; Weathers et al., 2013), questions about negative sexual experiences, mindfulness (Cognitive and Affective Mindfulness Scale-Revised (CAMS-R); Feldman et al., 2007), quality of life (World Health Organization Quality of Life: Brief Version (WHOQOL-BREF); The Whoqol, 1998), psychopathology (BSI-18; Derogatis, 2001), and therapeutic outcomes (Outcome Questionnaire (OQ-45); Lambert et al., 2004), will be assessed. As mentioned before, a subsample of participants will be invited to on-site laboratory sessions (at T1 and T2). Using a multimodal approach that combines EEG, behavioral tasks, thermal imaging, and self-report measures on affect (Positive and Negative Affect Schedule (PANAS; Watson, Clark, & Tellegen, 1988) and automatic thoughts (Sexual Modes Questionnaire - Thoughts Subscale (QMS; Nobre & Pinto‐Gouveia, 2003), this complementary part of the study will allow us to explore how brain activity, implicit cognitions, and interoceptive awareness contribute to intervention-related changes in sexual functioning and perception.

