## Data analysis

Descriptive statistics will be provided for demographic characteristics and outcome variables, including means and standard deviations for continuous variables and proportions for categorical variables. Independent sample t-tests and chi-square analyses will be conducted to evaluate potential baseline differences between participants assigned to the experimental and control groups to determine preliminary efficacy. The qualitative data collected in the final interview will be included in the analysis. For the data collected during the lab experiment, we will opt for a multimodal analytical approach. Behavioral and physiological data regarding sexual cognitions and interoception will be collected to explore underlying psychological and neurological processes and potential changes resulting from the intervention. Hence, for the within-subject factors (such as multiple time points or conditions in the ERP or thermal response experiments), rmANOVAs or Linear Mixed Effects (LME) models will be used for detecting overall differences across these conditions. Regression analyses will help in predicting outcomes, and correlations can offer insights into the strength and direction of associations. GMLL will allow us to model the random effects of individuals, accounting for the correlation among repeated observations and providing subject-specific insights. Differences between the experimental and control groups regarding secondary outcomes will also be analyzed. We will comply with the intention-to-treat (ITT) principle for comparisons between treatment groups.

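### Up to 20 of 35 intervention participants, and no waiting-list participants, attend laboratory sessions, so arm-1 retention and the between-arm estimates mix online-only with laboratory-exposed participants.

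*Protocol article*

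**What the plan says.** Under Participants and eligibility criteria, the protocol article takes the laboratory subsample from one arm: "A subsample of 20 participants from the intervention group will be invited to undergo an on-site laboratory data collection". Entry to it is restricted by age (18-40), right-handedness, preferences about the visual stimuli, and use of medication, alcohol or drugs.

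Recruitment, enrollment, and randomization describes the same group differently: "Randomization will also allocate a nested sample (n = 20) to an embedded assessment moment (T1 and T2"). No arm is named there. That section also sets the main allocation, "Participants will be randomly allocated 1:1 to the two study arms", and the content of the visits: EEG, an implicit association task, and a body-heat component, "Laboratory tasks will also include a physiological (thermography) plus self-reported body-heat sensations (genital temperature) assessments".

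Intervention delivery and assessment repeats T1 and T2 for the laboratory sessions. It uses T2 for the post-test of arm 1 only; the post-test of arm 2 is called T1rep. The same section lists among the primary outcomes "feasibility measures (i.e., recruitment, randomization, retention, and adherence rates"), and among the other measures self-reported interoceptive awareness, sexual function, pleasure and distress.

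Data analysis adds: "Differences between the experimental and control groups regarding secondary outcomes will also be analyzed", under the intention-to-treat principle. The sample-size paragraph says that the pilot is to supply effect sizes and attrition rates for planning the definitive trial.

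**The concern.** The laboratory sessions are research assessments, not part of the eight online modules. As described, only the intervention arm gets them, so they are a co-exposure that travels with the arm. Randomisation balances the participants, not the visits, and intention-to-treat analysis keeps each arm as it is, visits included.

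There are two plausible routes to the results:

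- **Retention.** An in-person appointment at T2 bears directly on whether someone is still in the study at T2. It may help, through contact and commitment, or hurt, through burden.
- **Self-reported outcomes.** The sessions direct attention to sexual response and bodily sensation, which the questionnaires also measure and which the programme's body-sensations module trains. The T1 session falls between the baseline and post-test questionnaires. The T2 session matters for T2 self-report only if it comes first, and the order is not given.

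At stake are the quantities that the pilot is meant to pass on: the attrition rate and the effect sizes. A definitive trial of an online programme would presumably not send over half of one arm to a laboratory.

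**Working it through.** **Inputs.** From the protocol article: N = 70, 35 per arm, 1:1; laboratory subsample 20, all from the intervention group; anticipated retention 70-75% (attrition 25-30%). The article gives no laboratory effect, so every effect below is an assumption.

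**1. The plan's own figures.** 2 × 35 = 70, as stated. 1 − 0.30 = 0.70 and 1 − 0.25 = 0.75, as stated. Expected completers per arm: 35 × 0.70 = 24.5 to 35 × 0.75 = 26.25.

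**2. Share exposed.** 20/35 = 57.1%, the maximum. At least 15/35 = 42.9% of the arm is online-only. If only 10 or 15 take up the invitation, the share is 10/35 = 28.6% or 15/35 = 42.9%. In the waiting-list arm it is 0%.

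**3. Timing.** Randomisation follows the online T1 assessment. A T1 laboratory session limited to the intervention group must then come after allocation, so after the baseline questionnaires. Baseline self-report is not affected, but the T1 session counts as exposure before the post-test.

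**4. Retention.** Shift in the arm rate = (20/35) × laboratory effect, in either direction.

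| Assumed laboratory effect on retention | Shift in arm-1 retention |
|---|---|
| ±5 points | ±2.9 points |
| ±10 points | ±5.7 points |
| ±20 points | ±11.4 points |

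If the arm shows 70%, online-only retention would be 70 − 5.7 = 64.3% for a +10 effect and 70 + 5.7 = 75.7% for a −10 effect.

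**5. Secondary outcomes.** The same weight applies to the arm difference: 0.571 × 0.1 = 0.06 SD; 0.571 × 0.2 = 0.11 SD; 0.571 × 0.5 = 0.29 SD.

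**6. Sampling error for comparison (95% half-widths).**

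- Arm-1 retention, n = 35: 1.96 × √(0.70 × 0.30/35) = 15.2 points; at 75%, 14.3 points.
- Arm difference, 35 v 35: 1.96 × √(2/35) = 0.47 SD. After 25-30% attrition: 1.96 × √(2/26.25) = 0.54 to 1.96 × √(2/24.5) = 0.56 SD.

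The shifts in steps 4 and 5 are smaller than these.

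**7. What a split by laboratory status can show.** Retention among 15 non-laboratory participants: 1.96 × √(0.70 × 0.30/15) = 23.2 points; at 75%, 21.9 points. Among 20 laboratory participants: about 19-20 points.

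**The case against.** Several arguments on the other side carry weight.

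- **The stronger reading fails.** A reader might infer that the trial measures FULLSENSE plus laboratory visits and not the online programme. It does not: at least 15 of 35 get the programme alone, and 20 is an invitation target under narrow criteria, so actual exposure may be well below 57%.
- **No upward bias is shown.** A reader might also infer inflated retention. Burden could equally lower it, and nothing in the article fixes the sign.
- **Not every outcome is equally exposed.** The T2 visit falls at the end of the programme, so it can reach module adherence only by anticipation; the T1 visit is the other route. No clear route to the usability score is apparent.
- **The article does not say how feasibility rates are computed.** It cannot be said to have chosen to pool the 20 without distinction. Silence on such tables is normal in a condensed protocol and is not the point here.
- **Contact is unequal anyway.** The intervention arm has psychologist guidance, an appointment and weekly progress review. But that support belongs to the guided programme under test; the laboratory visits do not.
- **The pilot disclaims efficacy inference, and its sampling error is larger than the likely shift.** Both are true. But sampling error shows in the confidence interval. This shift does not, and it passes into the planning figures.

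What remains is the stated design choice: the visits are confined to one arm.

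**Conclusion.** The point holds as a modest, cheaply addressed weakness. Up to 20 of 35 intervention participants and no controls have extra on-site sessions. Arm-1 retention and the between-arm secondary estimates are therefore averages over online-only and laboratory-exposed participants.

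The shift is (share attending) × (laboratory effect): about 6 points of retention for an assumed effect of 10 points, and about 0.11 SD for an assumed 0.2 SD, in either direction and at full uptake. Against half-widths of 14-15 points and 0.47-0.56 SD, it would not dominate the pilot's results. It matters because those results are meant to be carried forward.

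The two accounts of how the 20 are chosen also need reconciling: selective invitation within the intervention group, or allocation by randomisation with no arm named. The answer decides how comparable the non-laboratory group is. Even with random choice among eligible people in arm 1, that group would still contain everyone who fails the laboratory criteria.

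**What to change.** 1. **Order at T2.** Have the T2 online questionnaires completed before the T2 laboratory session. This removes that session's direct effect on self-report, though not any effect of the T1 session. Cost: a fixed task order.
2. **Show the split.** Report arm-1 retention and adherence in total and by laboratory status, descriptively. State that the non-laboratory group (about 15) is selected by the laboratory criteria and has a half-width of about 22-23 points. It cannot carry the scale-up statement alone; use it to qualify that statement.
3. **Sensitivity comparison.** Where the laboratory entry criteria were or can be recorded before randomisation, compare secondary outcomes between arms among laboratory-ineligible participants. This comparison is still randomised and free of laboratory exposure. Age is assessed at screening, so those over 40 can be identified in both arms without a new item. Other criteria may be unavailable for people already randomised, since the trial launched in May 2025. State the wide interval: if 15 per arm were ineligible (an assumption), the half-width would be 1.96 × √(2/15) = 0.72 SD.
4. **Reconcile the text.** Give one account of how the 20 are chosen and from which arm, and say when the T1 laboratory session takes place relative to randomisation.

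Downside: two extra tables with wide intervals and less freedom in scheduling T2.

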**Figure 1. F0001:**
[figure not shown]
FULLSENSE pilot feasibility randomized controlled trial participant flow diagram. *Note*. PRO = participant-reported outcome.

Based on attrition rates observed in similar 8-week online trials, we anticipate a retention rate of approximately 70–75% (i.e., a predicted attrition of 25–30%) (Zarski et al., 2022). To maximize participant engagement throughout the 8-week period, several retention strategies will be implemented. Specifically, participants will receive regular check-ins and support via email communication with the research team to address any technical or logistical issues and to promote adherence. In addition, weekly automated reminders will be sent to prompt module completion.

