As aforementioned, this feasibility pilot trial has several strengths, including its RCT design, the inclusion of diverse sexual dysfunctions (both male and female), the use of validated outcome measures, and its comprehensive and transdiagnostic nature. Nevertheless, some limitations must be acknowledged. While adequate for feasibility testing, the sample size may limit the generalizability of the findings and preclude definitive conclusions about efficacy. Initially designed for evaluative training courses, the platform may not be optimally suited for the program’s learning and reflection exercises, potentially impacting user experience, especially for smartphone users. Consequently, recruitment and retention of participants may present challenges, so future optimization of the platform for smartphone use might also be crucial. A key limitation of this protocol, inherent to its pilot nature, is the **small sample size (N = 70)**. While sufficient for assessing feasibility and generating preliminary effect sizes, the study is **not powered to draw definitive inferential conclusions** regarding the efficacy of the FULLSENSE intervention. The results must therefore be interpreted cautiously and strictly within the context of **viability and preparatory data** for a larger trial Also, the participatory design approach did not include its primary end users, which may influence acceptability and feasibility. We acknowledge the limitation that, due to its general design, the program may not fully reflect the specific, nuanced experiences of all sexual and gender minority groups, which may influence individual engagement. We clarify that future qualitative research will be essential to explore these differences in depth.

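### Many EEG/ERP trials per person do not make subtle intervention effects detectable or minimise between-person variability in a laboratory sub-study of 20 treated participants

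*Protocol article*

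**What the plan says.** The sample-size paragraph under Participants and eligibility criteria first says that 35 per arm was not chosen to give power for treatment efficacy. It then turns to the neurophysiology: "The study employs a within-subject design with a high number of trials per participant and fine-grained EEG/ERPs measures, which substantially increases statistical power". The next sentence reads "This approach allows for the detection of subtle intervention-related effects at the individual level and minimizes inter-individual variability". The paragraph closes by saying that the many repeated measurements give reliable estimates of within-person change despite a small sample. It gives no trial count, effect size, SD, significance level or power.

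On who is measured, the same section says "A subsample of 20 participants from the intervention group will be invited to undergo an on-site laboratory data collection". The recruitment section gives n = 20 and places the assessments at T1 and T2.

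Under Data analysis, "rmANOVAs or Linear Mixed Effects (LME) models will be used for detecting overall differences across these conditions", and a further model is to "model the random effects of individuals, accounting for the correlation among repeated observations". The Discussion says that the study as a whole is "not powered to draw definitive inferential conclusions" about efficacy. It does not mention the EEG statement.

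**The concern.** An intervention effect in the sub-study is a T1–T2 change averaged over people, so its precision depends on the number of people and on how much they differ in their change. A pre-post contrast removes stable differences in level between people. It does not remove differences in change, and recording more trials does not reduce them.

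A reader who accepts the paragraph could take a null EEG result as good evidence of no effect, or take a noisy positive one as evidence of mechanism. The article also offers itself as a blueprint for later digital sexual health research, so the statement may be copied into other designs.

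**Working it through.** **Inputs from the article.** Laboratory sample 20, from the intervention arm, with one session at T1 and one at T2. Retention 70–75%, stated for the whole trial in the paragraph after Figure 1. The article gives no power figure to reproduce.

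**Assumptions.** Two-sided 5% and 80% power. Trial-wide retention applies to the laboratory sample: 20 × 0.70 = 14 and 20 × 0.75 = 15 pairs. Effects are expressed as d_z, the mean change divided by the SD of change between people.

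**Step 1: what more trials do.** Set the between-person SD of true change to 1. With trial-noise SD r and m trials per session, the variance of the mean change is

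(1 + 2r²/m) / n.

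Only the second term shrinks as m grows. For illustration, with r = 10 (assumed) and n = 20:
- m = 200: SE = √((1 + 200/200)/20) = 0.316
- m = 1000: SE = √((1 + 200/1000)/20) = 0.245
- m unlimited: SE = √(1/20) = 0.224

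Trials help, but the SE cannot fall below 1/√n.

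**Step 2: the floor with unlimited trials.** Paired t-test, noncentral t:

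| Pairs | Detectable d_z, 80% power | Detectable d_z, 90% power | Power at 0.2 | Power at 0.3 | Power at 0.5 |
|---|---|---|---|---|---|
| 20 | 0.66 | 0.76 | 14% | 25% | 57% |
| 15 | 0.78 | 0.90 | 11% | 19% | 44% |
| 14 | 0.81 | 0.94 | 11% | 18% | 41% |

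A one-sided 5% test at 80% power gives 0.58, 0.68 and 0.70. By the normal approximation, 80% power for d_z = 0.3 needs (1.960 + 0.842)²/0.3² ≈ 88 completers.

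**Step 3: finite trials.** With r = 5 (assumed), the detectable change for 20, 15 and 14 pairs, in SDs of true change, is:
- 20 trials: 1.24, 1.46, 1.52
- 100 trials: 0.81, 0.95, 0.99
- 1000 trials: 0.68, 0.80, 0.83

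These approach the floor in Step 2 from above.

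**Step 4: other scale.** With equal SDs at T1 and T2, a change in baseline-SD units is d_z × √(2(1 − ρ)), where ρ is the test-retest correlation. For 20, 15 and 14 pairs the floor is:
- ρ = 0.5: 0.66, 0.78, 0.81
- ρ = 0.8: 0.42, 0.49, 0.51
- ρ = 0.9: 0.30, 0.35, 0.36

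The article gives no ρ.

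**Step 5: the individual level.** Many trials can show that one person's signal differs between two sessions. With one session before, one after and no control participants in the laboratory, that difference could equally come from time, retest or the session itself. It cannot be labelled intervention-related.

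**The case against.** Much of the paragraph can be defended.

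- **More trials do raise power when trial noise is large.** In Step 1, going from 200 to 1000 trials cuts the variance from 0.10 to 0.06, the same as raising n from 20 to about 33 (20 × 0.10/0.06). This stands. The general statement about power is fair up to a limit, and so is the closing sentence on within-person estimation.
- **The label within-subject.** A reader might infer that it is wrong for a two-arm trial, or that the power sentence contradicts the 35-per-arm statement. The documents support neither. The sub-study is measured twice in the same treated people, and the 35-per-arm sentence concerns efficacy in another sample. What remains is an unclear referent, because the sentence says the study where it means the sub-study.
- **Trials analysed as independent observations.** A reader might infer this as well. Data analysis points the other way, since it models random effects of individuals and the correlation among repeated observations.
- **The claim is about individuals, not group means.** The planned tests concern overall differences, and Step 5 shows why the individual reading does not rescue the claim.
- **The analysis also compares task conditions.** The T1–T2 calculation does not cover those contrasts. The disputed sentence, however, is about effects of the intervention, and these need the T1–T2 contrast.
- **The laboratory work is exploratory and the Discussion urges caution.** Both are true and they limit the consequence: no primary outcome or sample size depends on the sentence. Neither withdraws it.

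**Conclusion.** The point holds as a wrong statement about what the design can do. Two claims lack support: that subtle intervention-related effects are detectable, and that variability between people is minimised. With all 20 retained, the floor is about 0.66 SD of change however many trials are recorded. With 14–15 pairs it is about 0.78–0.81. Power for 0.3 SD is 18–25%.

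These figures rest on the assumed significance level and power, and the lower pair counts rest on applying trial-wide retention to the laboratory sample. It would go too far to say that only large effects can be detected: 0.66 is medium to large, and in baseline-SD units the floor could be lower if the test-retest correlation is high. On the change-SD scale, power for changes of 0.2–0.3 does not exceed 25% at any of these sample sizes.

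**What to change.** Revise the end of the sample-size paragraph under Participants and eligibility criteria:

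1. State that these sentences describe the laboratory sub-study (n = 20, intervention arm, T1 and T2), not the two-arm trial.
2. Delete the claims that subtle intervention-related effects can be detected and that variability between people is minimised.
3. Say instead that many trials improve the precision of each person's measurement only.
4. State that the sub-study is exploratory. Give the detectable range of about 0.66 SD of change with 20 pairs and 0.78–0.81 with 15–14, together with the assumptions (two-sided 5%, 80% power, trial-wide retention).
5. Say that results are reported as estimates with 95% confidence intervals, with the participant as the unit, in line with the random effects already planned under Data analysis. The expected half-width is t/√n: 2.093/√20 ≈ 0.47 SD of change with 20 pairs, and about 0.55–0.58 with 15–14.
6. Note that without control participants in the laboratory, T1–T2 changes are not attributed to the intervention.

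The cost is wording and a less favourable stated figure. Sample, procedures and budget do not change.
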